### Partner Support and Sustained Cessation

In a review of postpartum relapse prevention strategies, programs that involved the pregnant smoker’s partner were deemed necessary to maximize long-term cessation success [19]. To date, only one randomized controlled trial (RCT) has been conducted to examine the effect of partner support [20]. Participants were randomized to 3 groups: usual care, counseling support (6 counseling telephone calls; 3 during pregnancy, 3 postpartum), and counseling support combined with partner-support facilitated by a tailor-made “it takes two” booklet and video (partner was usually baby’s father who was also provided 6 separate counseling support telephone calls). No significant difference in participants’ smoking behavior was found between the groups. Interestingly, the authors found that positive support (behaviors characterized by cooperation and reinforcement of quitting behavior such as “compliment you on not smoking”) diminished linearly from baseline to 12 months postpartum and negative support (behaviors characterized by nagging and policing such as “comment on your lack of willpower”) decreased through pregnancy before increasing again postpartum.

The importance of the quality of support provided in partner support interventions has been found to be critical in promoting cessation among non-pregnant smokers [21]. In a study exploring the effect of positive and negative support behaviors on quit rates among female smokers, Cohen and Lichtenstein showed that women who reported receiving a higher ratio of positive supportive behavior compared to negative (using a shortened version of the Partner Interaction Questionnaire) from their spouse were more likely to quit. This emphasis on quality of support may explain why other studies found no effect for partner support [20-22].

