### Objectives

The purpose of this study is to determine whether providing incentives to both support person and expectant mother, if she is able to quit smoking, is more effective than providing incentives to expectant mother only, in promoting short- and long-term smoking cessation during pregnancy. In essence, the present study seeks to answer the question: “Can partners (eg, spouse) be incentivized to be more supportive and effective quit buddies to their pregnant smoking partners?”

Specifically, the study aims to determine whether (1) providing an incentive to both the support partner and expectant smoking mother to quit is more effective than providing an incentive to the pregnant smoker alone at promoting abstinence; (2) regardless of incentives, women who receive more positive cessation support from their partners, as measured by the Partner Interactive Questionnaire 20 (PIQ-20), are more likely to quit smoking; and (3) providing incentives for pregnant smokers to quit is more effective than “usual care” antenatal quit smoking services such as brief advice and referral to smoking cessation services (external telephone counseling and smoking cessation nurse) at promoting smoking cessation.

The primary outcome for the study is smoking status (ie, smoking or quit), as determined by self-report 7-day point prevalence, and carbon monoxide (CO) less than 7 particles per million (ppm) at the end-of-pregnancy time point. Secondary outcomes include effect of incentives on long-term (2 months and 12 months postpartum) abstinence and influence of the quality of partner support (positive compared to negative supportive behaviors) on smoking status.

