#### Partner Interaction Questionnaire

The Partner Interaction Questionnaire (PIQ) is used to gather information about the level of partner support [33]. It includes 10 positive (PIQ-POS) (eg, “Express pleasure at your efforts to quit”) and 10 negative (PIQ-NEG) (eg, “Comment on your lack of willpower”) partner behaviors that could be expressed towards a quitting partner. This questionnaire is completed at each study visit.

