### Planned Analyses

Analyses are planned to test each of the 4 hypotheses.

#### Hypothesis 1

The first hypothesis (H1) is that providing an incentive to both the support partner and expectant smoking mother to quit is more effective than providing an incentive to the pregnant smoker alone at promoting abstinence during pregnancy.

The quit rates of the treatment and control groups will be compared at the end-of-pregnancy time point (visit 2) using chi-square analysis. While no study to our knowledge has compared participant-only incentive with combined participant and support partner incentive, Donatelle et al [23] compared a usual care control group with an incentive plus partner incentive treatment group and found that at the end-of-pregnancy, 32% of treatment group participants had quit (n=105) compared with 9% in the control group (n=102), which indicates a large effect size (*χ*^2^=18.4, N=207, *d*=0.62) [23]. Since the control group in the present study is also receiving incentives, it is anticipated that the effect size may be moderate, rather than large. As such, to determine if there is a significant difference in proportion of women who have quit between control group and treatment group, with the power of .80 to detect an effect size of 0.30, the study will require a total sample size of 108.

#### Hypothesis 2

The second hypothesis (H2) is providing an incentive to both the support partner and expectant smoking mother to quit is more effective than providing an incentive to the pregnant smoker alone at promoting abstinence in the postpartum period.

As per H1 above, treatment and control group abstinence rates will also be compared at the end-of-study (visit 3) and at 12-months postpartum follow-up time points to determine the effect of incentivized partner support on postpartum abstinence. A multi-comparison adjustment will be applied to control for family-wise error.

#### Hypothesis 3

The third hypothesis (H3) is regardless of incentives, women who receive more positive cessation support from their partners (as measured by PIQ-20) are more likely to quit smoking.

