Participants, regardless of group allocation, will be regrouped to either PIQ-POS or PIQ-NEG, as determined by the ratio of positive compared to negative support they report receiving from their support partners. The abstinence rates of these regrouped PIQ-POS and PIQ-NEG participants will then be compared at 3 time points; end-of-pregnancy, end-of-study (2 months postpartum), and 12 months postpartum.

#### Hypothesis 4

The fourth hypothesis (H4) is providing incentives for pregnant smokers to quit is more effective than “usual care” antenatal smoking cessation support at promoting smoking cessation.

The quit rates of participating women will be compared to the average quit rate of a historical control of women receiving antenatal care by the Tasmanian Health Service from 2011 to 2015 [34].

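### H3 is worded as the amount of positive partner support but tested only by a two-group split on the positive-to-negative ratio, so a significant difference cannot by itself confirm it

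*Protocol article*

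**What the plan says.** Under Planned Analyses, Hypothesis 3 states that, whatever the incentive arm, "women who receive more positive cessation support from their partners (as measured by PIQ-20) are more likely to quit smoking". Aim 2 under Objectives says the same.

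The analysis then pools the two arms and places every woman in one of two groups, labelled PIQ-POS and PIQ-NEG. The criterion for the grouping reads: "as determined by the ratio of positive compared to negative support they report receiving from their support partners". After that step, "The abstinence rates of these regrouped PIQ-POS and PIQ-NEG participants will then be compared at 3 time points". Those are the visit late in pregnancy, the one about 2 months after birth, and the 12-month follow-up. No other H3 analysis is described, and the two subscales are nowhere analysed separately. The same labels, PIQ-POS and PIQ-NEG, serve both for the two 10-item subscales (section Partner Interaction Questionnaire) and for the two groups of women.

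Two other places explain the ratio. Objectives lists as a secondary outcome the "influence of the quality of partner support (positive compared to negative supportive behaviors) on smoking status". The section Partner Support and Sustained Cessation cites an earlier study of female smokers in which "women who reported receiving a higher ratio of positive supportive behavior compared to negative" were more likely to quit.

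**The concern.** H3 names one quantity and its analysis uses another. A woman can change group because her partner nags less, with no change in the positive support she receives. A difference in quit rates between the groups would nevertheless be reported as support for H3.

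The distinction has practical weight. The article's Conclusions say the findings may bear on the role given to support partners. Advice to encourage more and advice to nag less are different advice, and a two-group ratio comparison cannot separate them. The article itself gives reason to expect the two to behave differently: in the earlier randomised trial it describes, positive support declined steadily to 12 months postpartum, while negative support "decreased through pregnancy before increasing again postpartum".

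**Working it through.** **No plan figure to reproduce.** The article gives no sample size, power or cut-off for H3. The figure of 108 belongs to H1 and is used below only as the number of women.

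**Step 1: arithmetic on the ratio.** This assumes only non-negative scores.

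- Level is lost. Positive 30, negative 20: 30/20 = 1.5. Positive 3, negative 1: 3/1 = 3.0. The second woman has one tenth of the positive support and twice the ratio.
- Negative support alone can move a woman. Positive fixed at 20: 20/25 = 0.8 and 20/10 = 2.0. With a cut at 1 she changes group with no change in the quantity H3 names.
- Positive support is not ignored. At a fixed negative score above zero, the ratio rises with the positive score.

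**Step 2: how much this could matter.** Every input except N = 108 is assumed, because the article does not give the PIQ response scale, the score distribution or the cut-off. Inputs: each subscale 0 to 40; positive mean 24, negative mean 14, both SD 9, independent; logit of quitting = −1.1 + b(pos) × standardised positive score + b(neg) × standardised negative score, giving about 25% quit. Entries are the share of simulated trials significant at two-sided 5% in H3's direction, except that the joint test has no direction. Repeat runs agree within about 3 percentage points.

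| b(pos) / b(neg) per SD | Ratio > 1 | Ratio > median | Positive coefficient, both terms in model | Joint test of both terms | Continuous positive minus negative |
|---|---|---|---|---|---|
| +0.7 / 0 | 25% | 21% | 81% | 75% | about 50% |
| 0 / −0.7 | 25% | 51% | 2% | 74% | about 50% |
| +0.5 / −0.5 | 47% | 60% | 52% | 76% | 81% |

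- Second row: positive support has no effect, yet the ratio split appears to confirm H3 in a quarter to a half of trials. The positive coefficient does so in about 2%, close to the nominal 2.5% for one direction.
- First row: a median split of the positive score alone gives about 66%. Of the gap between 81% and 25%, dichotomising accounts for 81 − 66 = 15 points and the use of a ratio for 66 − 25 = 41 points.
- With a cut at 1, about 41% of the women placed in PIQ-POS have positive support at or below the median of all women. Membership therefore says little about amount.

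**Step 3: other assumed inputs.** Means 22 and 12, SD 8, log-odds 0.9 per SD, correlation between subscales 0 or 0.3. If only negative support matters, the ratio split appears to confirm H3 in 22% to 34% of trials (cut at 1) or 68% to 70% (median cut). If only positive support matters, it detects this in 11% to 36%, against about 87% for a median split of the positive score. The pattern is the same; the sizes depend on the inputs.

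**The case against.** The strongest reply is that the ratio is the intended construct. Objectives speaks of quality of support, positive set against negative, and the introduction cites a ratio finding and suggests that quality may explain null partner-support studies. H3's wording can also be read as support that is more positive on balance. On that reading, a partner who praises often and nags slightly more often is rightly not in the positive group, and a contribution from negative support is part of what is tested. Moving the whole test to the positive coefficient would then drop the construct. It could also cost power: 52% against about 60% for the median ratio split in the third row, and 37% against 67% at +0.4 / −0.6.

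This stands in part. It shows that the ratio is deliberate and that a single replacement test on the positive score is not the right remedy on both readings. It does not remove the mismatch: the article states an amount in aim 2 and H3, and a balance in the secondary outcome and the analysis. Even on the balance reading, the split throws away information and cannot separate the two sources.

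A reader might infer two stronger points that the documents do not support. One is that the ratio takes no account of how much positive support is given; Step 1 shows otherwise. The other is that the ratio fails for women reporting no negative behaviour. The article does not give the PIQ scoring, so whether a zero can occur is unknown. If it can, a cut at 1 still places zero negative with any positive support plainly in PIQ-POS. Only zero over zero and ties remain open: under the assumed distribution about 7% of women have a zero denominator but only about 0.03% are zero over zero. The cut-off and such rules are details an article commonly leaves to a fuller document.

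**Conclusion.** The point holds as a mismatch between H3's wording and its measure. The planned split loses the absolute level of positive support, discards information by dichotomising, and cannot attribute a difference in quit rates to more positive rather than less negative support. A significant PIQ-POS versus PIQ-NEG result therefore cannot by itself confirm H3 as worded.

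The conclusion on attribution follows from the ratio itself. The sizes (about 25% to 51% apparent confirmation when positive support has no effect, and 21% to 25% against 81% when only positive support matters) are illustrative and rest on assumed scoring, distributions, effects and cut-offs. The documents do not support saying that an H3 result would be wrong, only that it would be ambiguous.

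The weight is modest. H3 is a secondary, observational hypothesis, the study is powered on H1, and the primary conclusion does not depend on it.

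**What to change.** Make the H3 analysis a logistic model of abstinence at each of the three time points, with the positive and negative subscale scores as two separate continuous terms, and report both coefficients with confidence intervals. Then settle the meaning of H3 in advance:

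- If H3 means the amount of positive support, keep the wording and test the positive coefficient.
- If H3 means balance, reword it as positive relative to negative support, and test either a continuous positive-minus-negative score or both terms jointly. In the simulations the difference score does best when both subscales matter (about 81%) and worse when only one does (about 50%). The joint test stays near 75% throughout but has no direction, so it must be read with the two coefficients.

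Keep the ratio grouping as a descriptive summary for comparison with earlier work.

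No new data are needed, since both subscales come from the questionnaire already completed at each study visit. If about 25% of 108 women quit, there are about 0.25 × 108 = 27 events for two terms, which is workable; fewer are likely if abstinence falls by 12 months. The cost is a change of analysis wording and a result stated per scale point instead of as two quit rates.

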### Eligibility Criteria

Women who express interest in participating in the study (either self-refer or consent to a health professional forwarding their contact details to research staff) are contacted by research staff and screened for eligibility using a previously validated protocol [24]. To be eligible for study entry, women must be (1) pregnant (20 weeks gestation or less); (2) at least 16 years of age; (3) self-report as being a current smoker (“even a single puff in the last 7 days”); (4) attending routine antenatal care provided by the Tasmania Health Service or participating GP center (Tasmanian, Australia); and (5) be able to attend a minimum of 3 appointments at 1 of the 3 data collection sites across Tasmania (Launceston General Hospital, Royal Hobart Hospital, or Mersey Community Hospital). Women younger than 18 years (but 16 years or older) require the consent of their parent, guardian, or senior antenatal health provider to participate in the study.

Potential participants are excluded from study entry if they self-report as non-smoking (ie, “have not smoked, even a single puff in last 7 days”) or if they have a cognitive or intellectual impairment that will inhibit fulfillment of participation requirements (eg, completion of surveys and/or attend organized study appointments). Participants who are found to be “gaming” (eg, those who tell researchers they are pregnant and/or smoking untruthfully to enroll in study) are also excluded from further participation and their data discarded. All participants are asked to nominate and are encouraged to bring along to study visits a support person, preferably a person they co-habit with (eg, spouse, father of child, or family member).

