#### Enrolment Visit

During the enrolment visit (visit 1) participants are asked to complete a battery of questionnaires and provide 2 CO breath samples. Regardless of group allocation, participants are asked to nominate a support person (they are asked to have this person in mind when completing the Partner Interaction Questionnaire), preferably the person they are living with (eg, partner or family member), whose contact details are recorded along with the participant’s own details to assist with future correspondence. While no smoking cessation counseling is provided, participants are offered a resource pack for themselves and their support partner.

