#### 12-Month Follow-Up Questionnaire

The 12-Month Follow-Up Questionnaire is administered via telephone during the 12-month follow-up telephone interview. This marks the completion of study participation. Participants are asked to describe their smoking status, experience of being in the study, details of partner support of quit attempts, and their overall general well-being and that of their baby. If participants are quit, they are invited to return to the study center to verify.

Fetal growth and birth outcomes are also collected from babies of consenting participants (a separate consent form is provided seeking access to this information) including head circumference, femur length, heart/vascular data, birth weight, Apgar score (overall health at birth), gestational age, and digital medical records of neonatal intensive care unit (NICU) or respiratory admissions (if applicable). These data will be used for exploratory analyses to determine any associations with intervention effects.

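### Hypothesis 3 compares crude abstinence rates between two partner-support groups without requiring support to be measured before the outcome, and without adjusting for arm or dependence

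*Protocol article*

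**What the plan says.** In the protocol article, Planned Analyses, Hypothesis 3 states that "women who receive more positive cessation support from their partners (as measured by PIQ-20) are more likely to quit smoking". Women from both arms are pooled and regrouped as PIQ-POS or PIQ-NEG, "as determined by the ratio of positive compared to negative support they report receiving from their support partners". Their abstinence rates are then "compared at 3 time points; end-of-pregnancy, end-of-study (2 months postpartum), and 12 months postpartum". The passage gives no PIQ visit, cut-point or covariates. The only analysis checks described elsewhere (Sample Size and Checks) concern site and recruitment cycle.

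On timing, the section Partner Interaction Questionnaire says: "This questionnaire is completed at each study visit". That covers visits 2 and 3, where CO-verified status is also recorded (End-of-Pregnancy Visit, End-of-Study Visit). It also covers enrolment, where women name a support person and "they are asked to have this person in mind when completing the Partner Interaction Questionnaire". At that point every woman must "self-report as being a current smoker" (Eligibility Criteria). The 12-month telephone questionnaire asks for "details of partner support of quit attempts" but does not name the PIQ.

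The Objectives describe the related secondary outcome as the influence of support quality on smoking status, which is causal wording.

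**The concern.** Support is meant to be the cause and quitting the result, but some support content describes how a partner reacts to the woman's smoking. In the background section the article illustrates positive support with "compliment you on not smoking", which presupposes that she is not smoking. The negative example given for this trial's PIQ is a remark about weak willpower, which is more likely if she has not stopped. If the ratio comes from the visit at which abstinence is judged, a woman who has quit can fall into PIQ-POS because she has quit. H3 could then appear confirmed with no effect of support.

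Two features of the stated comparison add to this, whichever visit is used:

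- **Arm.** The treatment is intended to make partners more supportive. It also doubles the vouchers paid for abstinence, and the woman collects both if the partner is absent (Interventions). Arm can therefore change both support and quitting, yet it is neither adjusted for nor stratified on. Using the enrolment PIQ largely removes this path, because enrolment support is reported around the time of allocation. A visit 2 or visit 3 PIQ does not.
- **Two groups.** Cutting a graded score into two discards information in a study whose sample size was set for H1.

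**Working it through.** **Plan's own figure.** None is given for H3. The total of 108 belongs to H1 and is used here only as the trial size.

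**Step 1. Which readings are open?** Setting the sections side by side, the group could come from (a) the enrolment PIQ, (b) the PIQ at the outcome visit, or (c) an earlier follow-up visit or a summary over visits. Nothing in Hypothesis 3 excludes (b) for the end-of-pregnancy or 2-month comparison. At 12 months (b) is not available, because no PIQ is named there.

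**Step 2. Size of the problem under (a) and (b).**

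Inputs from the article:
- N = 108.
- Quit rate p = 32%, the treatment-group rate in the cited earlier incentive trial.

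Assumed inputs:
- Lower quit rate of 20%.
- Median split, Pearson chi-square at two-sided 0.05.
- No effect of support on quitting.
- Being quit shifts the reported support score by δ = 0.3, 0.5 or 0.8 SD.
- Correlation of 0.5 between the enrolment and later scores.

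Simulation, 20,000 trials per setting, proportion significant:

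| Quit rate | δ | Same-visit PIQ | Enrolment PIQ |
|---|---|---|---|
| 20% | 0 | 5.3% | 5.1% |
| 20% | 0.3 | 16.1% | 4.9% |
| 20% | 0.5 | 36.9% | 5.2% |
| 20% | 0.8 | 72.7% | 5.2% |
| 32% | 0 | 5.0% | 5.1% |
| 32% | 0.3 | 20.8% | 5.0% |
| 32% | 0.5 | 47.8% | 5.1% |
| 32% | 0.8 | 85.9% | 4.8% |

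For δ of 0.3 or more, nearly all the same-visit rejections favour PIQ-POS.

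**Step 3. Hand check of one cell (p = 0.32, δ = 0.5).** The median m of the mixed score solves p·Φ(δ − m) + (1 − p)·Φ(−m) = 0.5.
- This gives m = 0.158, with Φ(0.342) = 0.634 and Φ(−0.158) = 0.437. Check: 0.32 × 0.634 + 0.68 × 0.437 = 0.203 + 0.297 = 0.500.
- Quit rate in PIQ-POS: 0.32 × 0.634 / 0.5 = 40.6%. In PIQ-NEG: 0.32 × 0.366 / 0.5 = 23.4%. The simulation gave 40.5% and 23.5%.
- Noncentrality: λ = N × [(0.406 − 0.234)/2]² / [p(1 − p)]. With unrounded rates this is 3.63, so the chance of significance with 1 degree of freedom is 48%, as simulated.

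**Step 4. Cost of two groups.** For a normal score cut at c, the share of information kept is φ(c)² / [Φ(c)(1 − Φ(c))]. It is largest at the median: 0.399² / 0.25 = 2/π = 0.64. The loss is therefore at least 36%. At c = 0.5 SD the share kept is 0.58, and at 1 SD it is 0.44.

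**The case against.** The strongest reply is that the article never says the ratio comes from the outcome visits. Hypothesis 3 can be read as one fixed grouping followed by three comparisons. An enrolment PIQ exists, taken when all the women are smokers, and grouping on it keeps the error rate at about 5%. This stands. A reader might infer that the plan has committed itself to a same-visit split, so that being quit drives the grouping. The text does not support that, and the absence of a named 12-month PIQ counts against it for one of the three comparisons.

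Three further points also stand:
- The missing 12-month PIQ, and women who count as smokers but have no PIQ from a missed visit, are difficulties only under a same-visit split. They are not separate defects.
- Not all PIQ content depends on smoking status. The positive example listed for this trial's PIQ concerns pleasure at efforts to quit, which can apply to a woman still smoking. The compliment example comes from the account of an earlier trial.
- The SD shifts and the median split are not in the article. The cut could equally be positive above negative.

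It can also be said that PIQ visit, cut-point and covariates are details for an analysis plan, and that pooling over arms matches a question asked regardless of incentives. This stands only in part. The two-group split and the comparison of rates pooled over arms are written down as the method, not left open. Pooling does not remove the influence of incentives; adjusting for arm would serve that question better. A positive-to-negative ratio has precedent in the cited work on non-pregnant smokers, but that supports the ratio as a measure, not an untimed dichotomy.

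**Conclusion.** The point holds in a limited form. The stated H3 analysis is a crude two-group comparison serving a causal aim. It does not require support to be measured before the outcome and does not adjust for arm or dependence. It permits, but does not prescribe, a grouping shaped by the outcome. If the same-visit PIQ were used, reverse causation alone would yield a significant H3 in about 16% to 86% of trials, against about 5% with the enrolment PIQ. The width of that range comes from the assumed shift of 0.3 to 0.8 SD, with a median split and quit rates of 20% to 32%. The loss of at least 36% of the information assumes a normal score. The documents do not support the stronger statement that H3 will be biased. The change should be made, but H3 is secondary and the H1 comparison is not affected.

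**What to change.** 1. Define support from a PIQ completed before the outcome: visit 1 for end-of-pregnancy status; for the 2-month and 12-month outcomes, either visit 1, or visit 2 with visit-2 smoking status in the model.
2. Replace the two-group comparison with a logistic model in which PIQ-POS and PIQ-NEG (or their ratio) are continuous terms, together with arm and baseline dependence.
3. Keep any same-visit PIQ-POS versus PIQ-NEG comparison as a description of association, and label it so.

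The cost is analysis wording. The PIQ is already scheduled at enrolment and dependence is in the Baseline Questionnaire, so no new data are needed.

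There are three downsides. Enrolment support is less proximal to the support given during the incentive period. Adjusting for visit-2 smoking removes any effect of earlier support that acts through end-of-pregnancy abstinence. H3 also stays observational: time order deals with reverse causation, but confounding by factors such as partner smoking can remain, and the report should say so.
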